**Fig. 1 Fig1:**
[figure not shown]
Overview of the patient pathways

### Sample size

Previous studies [28] report an approximately 10 point drop in SIAS for standard treatment with in vivo exposure. However, a 20 point drop has been observed for CBT with VR-based exposure [28] with standard deviations around 15 points in all treatment groups. We calculated effect sizes and found that 38 subjects are required in each group to detect if VR treatment is significantly better than standard treatment with in vivo exposure in a t-test with 80% power at the 0.05 significance level using a two-sided hypothesis. However, patients in the VR relaxation group continues in one of the exposure groups, so only 76 subjects need to be recruited. To compensate for a possible 10% drop-out rate we plan to recruit 90 patients.

### Interventions

A treatment manual based on Bouchard and colleagues’ adaptation [28] of the model and approach of Clark & Wells [11, 49] and Craskes Inhibitory Learning Approach [50, 51] will be applied for therapy. Treatment will be conducted by two clinical psychologists who will receive supervision every second week. Ten percent of the sessions will be audio recorded to ensure adherence to the manual. Recorded sessions will be chosen evenly across the different stages of treatment to ensure that all aspects of the treatment are represented when adherence is controlled. Treatment will be conducted for 10 consecutive weekly 60 min sessions. In the first two treatment conditions sessions are scheduled as follows: Session one: Building a therapeutic alliance and psycho-education about social anxiety and safety and avoidance behaviors. Session two to four: Cognitive restructuring. Session five to nine: Exposure in either in vivo or VR. Session 10: Relapse prevention. To ensure a fair comparison of the effect of VR and in vivo exposure, these treatment arms are identical except for exposure. All exposure happens in session, and whereas the exposure scenarioes in the CBT with VR-based exposure arm are limited to the scenarios mentioned below,there is a free choice of situation in the in vivo arm. This is to ensure a treatment as close to treatment as usual as possible in this arm. A recent meta-analysis found between-session interventions to be a significant moderator of attrition in both in vivo and VR-based exposure treatment [52]. Thus, to reduce dropout rate, and to adapt to treatment as usual at the mental health services in the region, homework is encouraged.

### Cognitive behavioral therapy with virtual reality based exposure

CBT with VR-based exposure will use 360° 3D videos with three scenarios: a) riding a bus, b) going to a school cafeteria and c) a job interview. These scenarios were chosen based on clinical experience and frequently reported difficult situations in the literature [28, 38]. The order of the scenarios is jointly decided by the patient and therapist. In the videos, the patients can make choices which determine the further course of the exposure scenario. For example, in the bus scenario, the system informing the passengers about the upcoming bus stop is out of order. Therefore, the patient has to ask the driver to tell when this is his or her stop to exit, when they reach the relevant stop. Depending on whether or not the patient decides to do so, the video will skip to one of two alternative directions of the scenario. During the VR exposures the therapist will also motivate the patient towards acting in ways they consider socially unacceptable or threatening (such as sneezing or putting a napkin on his/her head) to elicit fear of ridicule, and to help the patient learn to bend their rigid rules for social interaction.

### Cognitive behavioral therapy with in vivo exposure

In vivo exposure consists of therapist-guided exposure which takes place either inside or outside the therapist’s office with active modelling from the therapist in early sessions.. Similarly to the VR-based exposure during in vivo exposure the therapist will motivate the patient towards acting in ways they consider socially unacceptable or threatening.

### Virtual reality relaxation therapy

VR relaxation therapy will consist of a 360° 3D scenario of swimming with dolphins, created by the dolphin swim club (www.thedolphinswimclub.com). Swimming with real wild dolphins has been shown to have a positive effect on anxiety, although not specifically on SAD [53].

### Assessment

Diagnostic assessment will be conducted with the short version of the Present State Examination (PSE) supplemented with the anxiety section from the full version. PSE is a semi-structured interview, intended to provide an objective evaluation of present mental disorders. It contains 140 items, each scored on a 3-point or 4-point scale [54].

### Primary and secondary outcome measures

The primary outcome is degree of severity of SAD symptoms, which will be assessed at baseline, before exposure sessions, post-treatment and at the 6 months follow-up, with the Social Interaction Anxiety Scale (SIAS). SIAS is a measure of anxiety in social interactional situations and consist of 20 items scored 0–4. The total score range from 0 to 80 with a score higher than 43 indicating that SAD is probable [47]. The scale has been used and validated in international research, has good psychometric properties [47, 55], and focus on the interactional aspects of SAD, more so than on situations in which the person may be observed or scrutinized by others.

As a measure of general functioning at baseline, post-treatment and at the follow-up we use the EQ-5D-5 L. The EQ-5D-5 L is a standardized instrument for measuring generic health status [56, 57]. To study the practical and financial resources needed for exposure sessions, we include the questionnaire ‘Specific Work for Exposure Applied in Therapy’ (SWEAT). SWEAT measures cost and efforts required to conduct exposure sessions, and is filled out by the therapist after each exposure session [58]. As a measure of the therapeutic alliance we use the Working Alliance Inventory-Short Revised (WAI-SR) questionnaire, which assesses three key aspects of the therapeutic alliance: (a) agreement on the tasks of therapy, (b) agreement on the goals of therapy and (c) development of an affective bond [59].

### Other measures

Symptoms of ADHD and severity of autism spectrum disorder (ASD) characteristics will be assessed at baseline with the adult ADHD self-report scale (ASRS v1.1) [60] and the Social Responsiveness Scale (SRS-2) [61] respectively. Both ADHD and ASD are highly comorbid with SAD, and both are characterized by frequent social difficulties [62, 63]. Although patients with a diagnosis of ADHD are excluded, subsyndromal symptoms might complicate treatment. Alcohol and drug use will be assessed with the Alcohol Use Disorders Identification Test (AUDIT) [64] and the drug use disorders identification test (DUDIT) [65] respectively. Depressive symptoms will be assessed with the Beck Depression Inventory-II (BDI-II) [66], which is the most widely used instrument for detecting depression. (see Table 1).

**Table 1 Tab1:** Overview of measurements

	Instrument	Items	Screening baseline	Before exposure sessions	Weekly at exposure sessions	Post-treament	Follow-up
SAD	SIAS	20	+	+	–	+	+
Diagnoses	PSE	140	+	–	–	–	–
Cost and efforts required to conduct exposure sessions.	SWEAT	11	–	+	+	–	–
ASD characteristics	SRS-2	65	+	–	–	–	–
ADHD	ASRS	18	+	–	–	–	–
General functioning	EQ-5D-5 L	26	+	+	–	+	+
Working Alliance Inventory	WAI-SR	12	**–**	–	**–**	**+**	**–**
Alcohol use	AUDIT	10	**+**	+	**–**	**+**	**–**
Substance use	DUDIT	11	**+**	**+**	**–**	+	**–**
Depression	BDI-II	21	**+**	+	**–**	**+**	**–**

### Statistical methods

The effect of the treatment will be analyzed using a linear mixed effects (LME) model with the SIAS score as the outcome and treatment group and assessment point (baseline, before exposure sessions, post-treatment and six months follow-up) as the independent variables, allowing intercepts to vary between patients. The moderating effect of ADHD symptoms severity, autism spectrum characteristics, depressive symptoms, alcohol and drug use on the treatment outcome will be investigated by including them as covariates in the regression. Comparisons for the SWEAT will be performed with t-tests, set two-tailed.

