### Aims and hypotheses

The aims of the study that will use the clinical protocol described in the paper are to develop a complete program of CBT with VR exposure based on 360° videos for adult patients suffering from SAD, and to evaluate the treatment effect on SAD symptoms. We plan to compare a group receiving CBT with VR-based exposure immersed in an environment based on 360 videos stimuli to a group receiving CBT with in vivo exposure and a group receiving VR relaxation treatment. Having VR relaxation treatment as control group is methodologically superior to a comparison to a waiting list and controls for any placebo effect.

It is hypothesized that:
CBT with VR-based exposure will significantly reduce symptoms of SADCBT with VR-based exposure will be more effective than both CBT with in vivo exposure and VR relaxation therapy at the end of treatmentAn effect on symptom reduction will sustain at 6 months follow-up

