### Randomization and blinding

Patients are randomly assigned (by gender, age and baseline severity of SAD) to one of the following three arms in ratio 1:1:1 via the computerized randomization function in REDCap: 1) Individual CBT with VR-based exposure in session 2) Individual CBT with in vivo exposure in session or 3) Individual VR relaxation therapy. Assignment will be kept blind for patients and clinicians until the first exposure session. An equal number of patients will be assigned to each group, but at the end of treatment patients in the third group will be randomly re-allocated to one of the two former groups. This reallocation is done to reduce the total number of patients needed to be recruited, and to avoid the ethical problem of not offering effective treatment. Six months after end of treatment the patients in group 1 and 2 will be re-assessed. There will not be a follow-up assessment of the patients in group 3, as they are re-allocated after week 10 (see Fig. 1).

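### The primary mixed model is written without a group-by-assessment term or an end-of-treatment contrast; fitted literally, it does not estimate the end-of-treatment difference that the trial is meant to test.

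*Protocol article*

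**What the plan says.** Under Statistical methods, the protocol article describes a linear mixed effects model "with the SIAS score as the outcome and treatment group and assessment point" as predictors. It lists the assessment points as "baseline, before exposure sessions, post-treatment and six months follow-up) as the independent variables" and describes the random part as "allowing intercepts to vary between patients". No product of group and assessment point, no adjustment for baseline and no contrast at a given assessment is named. The next sentence treats moderators in the same way: their effect "will be investigated by including them as covariates in the regression".

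Under Aims and hypotheses, VR-based CBT "will be more effective than both CBT with in vivo exposure and VR relaxation therapy at the end of" treatment. Under Sample size, the trial is sized by a two-sided t-test on a 20-point against a 10-point SIAS drop with SD 15, which gives 38 per group.

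The timing of the contrast between the two CBT arms is also fixed. Under Interventions, "these treatment arms are identical except for exposure", and the schedule reads "Session five to nine: Exposure in either in vivo or VR". Under Randomization and blinding, "Assignment will be kept blind for patients and clinicians until the first exposure session". The same section gives the relaxation arm no six-month assessment.

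**The concern.** The hypothesis concerns one time point and the sample size concerns a difference in change. When baseline is one of the outcome values, a difference in change is a group-by-assessment contrast. A model with group and assessment point as separate terms instead holds the group difference equal at every visit, including baseline, where randomisation makes its expected value zero.

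For VR-based versus in vivo CBT, the before-exposure visit is also a zero-difference visit by design: the first four sessions are common to both arms and assignment is concealed until exposure begins. Averaging these two visits with the later ones dilutes the effect.

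Two things are at stake. A real benefit of the planned size could be reported as non-significant. And if the treatment parameter stays unnamed, the main effect, an interaction or the contrast at any visit could be chosen once the data are known.

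**Working it through.** **Inputs from the protocol article.** Difference in drop 20 − 10 = 10 points; SD 15; two-sided 0.05; 80% power; 38 per group (Sample size). Four assessments and a random intercept only (Statistical methods). The CBT arms diverge at session five (Interventions).

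**Assumptions not in the document.** Within-patient correlation ρ of 0.3 to 0.8, equal between all visits; 15 is the per-visit SD; complete data; VR-based minus in vivo differences of 0, 0, 10, 10 at the four visits, so that the benefit is fully kept at six months.

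**1. The plan's own figure.** The normal approximation gives 36 per group and the exact t-test 37, against 38 stated, so the figure is reproduced. At 38 per group the t-test has 81.8% power.

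**2. What the literal model estimates.** With complete data and a random intercept, the group coefficient is the plain mean of the visit differences: (0 + 0 + 10 + 10)/4 = 5 points. This does not depend on ρ.

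**3. Its power.** The SD of a patient's four-visit mean is 15·√((1 + 3ρ)/4). For ρ = 0.5 it is 15·√(2.5/4) = 11.86. Power from the noncentral t with 38 per group and a 5-point difference:

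| ρ | SD of mean | Power |
|---|---|---|
| 0.3 | 10.34 | 55% |
| 0.4 | 11.12 | 49% |
| 0.5 | 11.86 | 44% |
| 0.6 | 12.55 | 40% |
| 0.7 | 13.21 | 37% |
| 0.8 | 13.83 | 34% |

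Reaching 80% with this coefficient would take 69, 90 or 111 per group at ρ = 0.3, 0.5 or 0.7. In 200 simulated fits at ρ = 0.5, the additive model gave a mean coefficient of −4.9 with 42% power. The post-treatment interaction term gave −9.9 with 84%.

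**4. Post-treatment contrast.** The target is the full 10 points.
- Raw change from baseline: SD = 15·√(2(1 − ρ)). At ρ = 0.3 this is 17.7 and power is 68%; at 0.4, 74%; at 0.5, SD 15.0 and 82%; at 0.6, 89%.
- Baseline-adjusted: SD = 15·√(1 − ρ²). At ρ = 0.3 this is 14.3 and power is about 85%; at 0.5 it is 13.0 and about 91%.

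**5. Sensitivity of the literal model.**
- Benefit wanes to 5 points at six months: coefficient (0 + 0 + 10 + 5)/4 = 3.75, power 35% to 22% over ρ = 0.3 to 0.8.
- Only the three visits up to post-treatment: 10/3 = 3.3 points, power 26% to 18%.
- For the coefficient to equal 10, the six-month difference would have to be 30 points: (0 + 0 + 10 + 30)/4 = 10.
- If 15 is the SD of change and not the per-visit SD: power 69%, 44% and 24% at ρ = 0.3, 0.5 and 0.7, against 82% for the change contrast.

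**The case against.** The strongest reply is that the section is shorthand. A condensed article often lists the factors of a mixed model and leaves product terms and contrasts to a fuller document. The section never says that the model is additive. The moderator sentence supports this reading: moderation needs an interaction with treatment, yet only covariates are mentioned. The abstract, hypotheses and sample size all speak of reduction or of the end of treatment, and only an interaction model fits them all.

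Much of this stands. A reader might infer that the investigators chose a main-effects analysis. The document does not establish that, and a full analysis plan may name the interaction. But the section goes further than naming a method: it sets out the outcome, predictors, assessment points and random structure of the primary model, and followed as written it answers a different question.

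Three further limits also stand:
- It is tempting to say that most of the planned power is lost. At correlations of 0.4 to 0.5 it falls from 82% to 49% or 44%, a loss of less than half. At 0.3 it is still 55%, so a non-significant result is not the likelier outcome at every correlation.
- An interaction tested as raw change from baseline is not better everywhere: it has 68% power at 0.3, below the planned 80%, and at 0.2 both analyses have 62%.
- The argument about the before-exposure visit covers VR-based versus in vivo CBT only. Relaxation may differ from CBT earlier, although baseline dilutes that comparison too. The missing six-month value in the relaxation arm is by design, and no bias in the comparison of the CBT arms follows from it.

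**Conclusion.** The point holds as a badly fixed primary analysis. As written, the model's only treatment parameter is a four-visit average, which is neither the end-of-treatment difference in the hypotheses nor the difference in drop behind the sample size. Under the protocol's 10 points, SD 15 and 38 per arm, that parameter is 5 points, with power of about 55% to 34% for correlations of 0.3 to 0.8, against 82% for the planned t-test.

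The halving is independent of the correlation. It does depend on the assumed 10-point difference at six months and on no interaction being fitted. The power figures depend also on the assumed correlation and on reading 15 as a per-visit SD, which the document does not settle. The document does not show that the investigators intend the additive model; it shows that the stated model leaves the primary test unnamed.

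**What to change.** State the model as group + assessment point (categorical) + group × assessment point with a random patient intercept, preferably with baseline SIAS adjusted for or constrained equal across arms. Adjustment matters because raw change from baseline falls below 80% power at correlations under about 0.5.

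Then name the estimates in order:
1. Primary: VR-based CBT minus in vivo CBT at post-treatment.
2. Second comparison: VR-based CBT minus relaxation at post-treatment.
3. Secondary: the six-month contrast, between the two CBT arms only.

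If an analysis plan already says this, the published description should be brought into line with it. The cost is a few lines in Statistical methods, settled before the data are analysed. No new data, visits or patients are needed.

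### The SIAS mixed model names only a random intercept, so it assumes equal variance and correlation across four unevenly spaced assessments; if that fails, standard errors of change are misstated, most plausibly too small at six months

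*Protocol article*

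**What the plan says.** The Statistical methods section specifies a "linear mixed effects (LME) model with the SIAS score as the outcome", with treatment group and "assessment point (baseline, before exposure sessions, post-treatment and six months follow-up) as the independent variables", and closes the specification with "allowing intercepts to vary between patients". It mentions no random slope, residual correlation structure, visit-specific variance or robust standard error.

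The assessments are not evenly spaced. Under Interventions there are 10 weekly sessions, with exposure in sessions five to nine, so the second assessment comes about four weeks in and the third at about week 10. Under Randomization and blinding, "Six months after end of treatment the patients in group 1 and 2 will be re-assessed".

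The Sample size section gives the only information on spread: "standard deviations around 15 points in all treatment groups". It does not break this down by visit and gives no within-patient correlation.

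**The concern.** A random intercept with independent residuals gives SIAS the same variance at every assessment and the same correlation between every pair. Baseline is then taken to correlate as strongly with a score some 36 weeks later as with one four weeks later. Nor can the model show two pre-exposure scores agreeing with each other more closely than with the post-exposure scores, which would happen if patients respond differently to exposure.

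The model estimates one residual variance, averaged over all pairs of visits, and uses it for every change. Where a particular pair differs from that average, the standard error for that change is wrong. Too small a standard error gives too many false positives and confidence intervals that are too narrow. Too large a one wastes power in a trial sized at 80%.

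**Working it through.** **The plan's own figure first.** The inputs are "approximately 10 point drop in SIAS for standard treatment with in vivo exposure", "a 20 point drop has been observed for CBT with VR-based exposure", an SD of 15, and "80% power at the 0.05 significance level using a two-sided hypothesis". The difference is 20 − 10 = 10 points.

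n per group = 2 × (1.96 + 0.84)² × 15² / 10² ≈ 35.3, so 36 with the normal approximation. The exact t calculation gives 37. The stated 38 gives 81.8% power by the exact t calculation. The figure is reproduced to within two patients, and it does not depend on the mixed model's covariance.

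**Formula.** Take complete data, two arms, four visits, a group-by-assessment model and no true effect. The random-intercept fit estimates the residual variance as (mean variance − mean covariance) over the visits, and the variance of any change as twice that. With constant SD:

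- SE ratio (model / true) for change from baseline to visit t = √[(1 − mean correlation over the 6 pairs) / (1 − correlation of baseline with t)]
- true two-sided alpha = 2 × [1 − Φ(1.96 × ratio)]

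**Example A: first-order autoregression by visit order, correlation 0.8 between neighbours.** The mean correlation is (3 × 0.8 + 2 × 0.64 + 0.512) / 6 = 0.6987.

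- End of treatment: √(0.3013 / 0.36) = 0.915, alpha 0.073.
- Six months: √(0.3013 / 0.488) = 0.786, alpha 0.124.

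**Example B: decay with calendar time, 0.9 per four weeks, visits assumed at weeks 0, 4, 10 and 36.** The six correlations are 0.900, 0.768, 0.387, 0.854, 0.430 and 0.504, with mean 0.641.

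- End of treatment: √(0.359 / 0.232) = 1.25, alpha 0.015.
- Six months: √(0.359 / 0.613) = 0.77, alpha 0.133.

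In example B the distant six-month pairs inflate the pooled residual, so the shorter change gets a standard error that is too large.

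**Range over assumed structures, SD 15 throughout.** Entries are SE ratio (true alpha).

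| Assumed correlation | Baseline to end of treatment | Baseline to six months |
|---|---|---|
| Compound symmetry | 1.00 (0.050) | 1.00 (0.050) |
| Visit order, 0.5 | 0.93 (0.069) | 0.86 (0.092) |
| Visit order, 0.7 | 0.92 (0.072) | 0.81 (0.113) |
| Visit order, 0.8 | 0.91 (0.073) | 0.79 (0.124) |
| Calendar time, 0.5 per 4 weeks | 1.00 (0.050) | 0.91 (0.075) |
| Calendar time, 0.8 per 4 weeks | 1.15 (0.025) | 0.81 (0.114) |
| Calendar time, 0.9 per 4 weeks | 1.25 (0.015) | 0.77 (0.133) |
| Pre/post blocks: 0.8 within, 0.6 across | 0.91 (0.074) | 0.91 (0.074) |
| Noisier pre-exposure visit (0.5 with the others, 0.6 elsewhere) | 1.06 (0.038) | 1.06 (0.038) |

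**Cost in power when the standard error is too large.** Suppose a contrast would have 80% power with the right standard error, so the expected z is 1.96 + 0.84 = 2.80. At a ratio of 1.25 the effective critical value is 1.96 × 1.246 = 2.44, and power falls to Φ(2.80 − 2.44) = Φ(0.36) ≈ 0.64.

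**Simulation check.** REML fits with 38 per arm, 10% dropout and 400 runs per structure:

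- Visit-order correlation 0.7: model SE 3.28 against an empirical 3.55 at end of treatment (9.0% rejections) and 3.85 at six months (11.5%).
- Compound symmetry: 5.5% and 4.2% rejections.

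The Monte Carlo error of a rate near 10% is √(0.1 × 0.9 / 400) = 1.5 percentage points, so these agree with the formula in direction and rough size.

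**Arm difference at a single visit, rather than in change.** Here the ratio is √(mean variance / variance at that visit), which is 1.00 with a constant SD. It would be 0.88 (alpha 0.085) at the later visits if SD rose as 10, 12, 15, 15, and 1.13 (alpha 0.027) if it fell as 15, 15, 12, 12. The article supports neither pattern.

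**The case against.** The strongest objection is that none of the covariance inputs comes from the article. It gives no correlation, and its one SD is common to all groups, which is no evidence of growing variance. That stands: every ratio above is conditional, and there is no error if compound symmetry is true.

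A reader might infer that the standard errors are too small at both end of treatment and six months. The article does not support this. Uneven spacing is the reason to doubt compound symmetry, and once decay follows calendar time rather than visit number, the end-of-treatment test is conservative or unaffected. Nor can the anti-conservative result be rescued by fitting only the three visits up to week 10, because the stated model includes all four.

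A reader might also tie the six-month error to a between-arm test. The third hypothesis says only that an effect on symptom reduction will persist, and names no comparison of arms at that point.

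It can also be said that the residual structure or robust standard errors may sit in a fuller document. That is possible, since a random intercept is compatible with either. But the article does not leave the within-patient structure open. It states one, and as stated, with the usual independent residuals, that structure is compound symmetry. The point concerns a stated choice, not a missing detail.

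Finally, a random intercept is a common and legitimate model for a trial of this size. True, but four fixed assessments in 90 patients can support a less restrictive one at little cost.

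**Conclusion.** The point holds as a conditional weakness. The stated model rests on compound symmetry over four unevenly spaced assessments, and its standard errors for change are right only if that holds.

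- **Six months:** under every decaying-correlation structure examined, with SD 15, the model standard error for change from baseline is too small, at 0.77 to 0.91 of the true value (alpha about 0.075 to 0.13). A noisier middle visit without decay reverses this slightly (1.06).
- **End of treatment:** the direction is not established. The ratio is 0.91 to 0.93 under visit-order decay and 1.00 to 1.25 under calendar-time decay. It would therefore be wrong to say that the VR versus in vivo comparison at end of treatment is anti-conservative.

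These figures assume two arms, complete data, a group-by-assessment interaction, independent residuals and, for calendar decay, visits at weeks 0, 4, 10 and 36. This is a cheap improvement, held with moderate confidence.

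**What to change.** Fit SIAS with treatment group, assessment point and their interaction, and an unstructured within-patient covariance over the assessments, by REML with Kenward-Roger degrees of freedom. State in advance a simpler structure to use if the model does not converge, for example heterogeneous Toeplitz. Keep the random-intercept model as a sensitivity analysis.

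The cost is in analysis wording only: 4 × 5 / 2 = 10 covariance parameters instead of 2, and slightly fewer degrees of freedom. Compound symmetry is a special case of the unstructured form, so little is lost if the present assumption is right.

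### Moderation is to be examined by entering variables as covariates; applied as written, this tests whether they predict SIAS, not whether they change the treatment effect

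*Protocol article*

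**What the plan says.** The Statistical methods section describes a linear mixed model for the SIAS score with "treatment group and assessment point (baseline, before exposure sessions, post-treatment and six months follow-up) as the independent variables", "allowing intercepts to vary between patients". The next sentence sets a second question, "The moderating effect of ADHD symptoms severity, autism spectrum characteristics, depressive symptoms, alcohol and drug use on the treatment outcome", and gives its method: this "will be investigated by including them as covariates in the regression". No product of any of these variables with treatment, or with treatment and assessment point, appears anywhere in the article.

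The Other measures section explains the interest in ADHD and autism traits: "subsyndromal symptoms might complicate treatment". Table 1 shows all five variables measured at baseline. The ADHD and autism scales (ASRS, SRS-2) are measured only then. The depression, alcohol and drug scales (BDI-II, AUDIT, DUDIT) are repeated before the exposure sessions and at post-treatment. None of the three hypotheses under Aims and hypotheses concerns moderation.

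**The concern.** The section names a target and then fixes a method that does not estimate it. A moderator is a variable across whose values the treatment effect differs. A covariate entered alone has one slope, shared by all arms, so the fitted treatment effect is the same at every value of that variable. Such a model cannot show moderation in either direction.

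Two errors follow if the sentence is carried out literally and the covariate result is read as the answer. A variable that goes with higher or lower SIAS in every arm alike would be called a moderator. A variable that raises the benefit of one exposure format and lowers that of the other could go unseen. The first is a realistic risk, because the article itself describes ADHD and autism as highly comorbid with social anxiety disorder. In the mixed model the covariate slope is also averaged over assessment points, including baseline, so an association that existed before any therapy would be enough to make it significant.

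What is at stake is any statement about which patients do better with VR or with in vivo exposure.

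**Working it through.** **Inputs from the Sample size section.** SIAS falls: "approximately 10 point drop in SIAS for standard treatment with in vivo exposure", and "a 20 point drop has been observed for CBT with VR-based exposure", so the difference is 10 points. SD 15, 38 per group, 80% power, two-sided 0.05, 10% drop-out, 90 recruited.

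**The plan's own figure.** n per group = 2 × (1.960 + 0.842)² × 15² / 10² = 35.3, so 36. The t-test calculation gives 36.3, so 37. The stated 38 has 81.8% power and is reproduced to within two patients. The two exposure groups make 76; 90 recruited less 10% leaves 81. These are the two sample sizes used below.

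**What each term estimates.** Let G = ±½ for the two exposure arms, X the candidate variable in SD units, and Y = a + bG + cX + dGX + error.
- The treatment effect at X is b + dX, so moderation is d.
- The slopes of X in the two arms are c − d/2 and c + d/2, and their average is c.
- If GX is left out and the arms are of equal size, the coefficient of X estimates c. It carries no information on d.

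**A predictor that does not moderate (d = 0), by correlation.** The article gives no correlations; 0.2 and 0.3 are assumed. Power by Fisher's z = Φ(atanh(r) × √(n − 3) − 1.960).

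| r | n | atanh(r) × √(n − 3) | Probability that the covariate term is significant |
|---|---|---|---|
| 0.3 | 76 | 0.3095 × 8.544 = 2.645 | 0.753 |
| 0.3 | 81 | 0.3095 × 8.832 = 2.734 | 0.780 |
| 0.2 | 76 | 0.2027 × 8.544 = 1.732 | 0.410 |
| 0.2 | 81 | 0.2027 × 8.832 = 1.790 | 0.433 |

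A valid interaction test rejects in 5% of trials in every row.

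**Simulation of both terms.** Two arms of 38, residual SD 15, difference 10, standardized covariate, 4,000 runs per row; slopes assumed. A slope of 5 points per SD is a within-arm correlation of 5/√(5² + 15²) = 0.32, so it matches the upper rows above.

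| Truth | Covariate term significant | Group × covariate significant |
|---|---|---|
| Neither (c = 0, d = 0) | 5% | 5% |
| Predictor only, c = 5 | 79% | 5% |
| Predictor only, c = 7.5 | 98% | 5% |
| Moderator only, d = 5 | 5% | 28% |
| Moderator only, d = 10 | 6% | 78% |
| Moderator only, d = 15 | 7% | 98% |

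Closed-form check for d = 10: SE = 15 × √(1/38 + 1/38) = 3.44; 10/3.44 = 2.91; Φ(2.91 − 1.96) = 0.83. This normal approximation is close to the simulated 78%.

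**Repeated-measures check.** A random-intercept model with three assessment points, two arms of 38 and a total SD of about 15 was run 200 times per scenario. For a predictor of 5 points per SD with no moderation, the covariate term was significant in 92.5% of runs and the group × time × covariate term in 5.5%. With no effect of the covariate at all, both were significant in 7%, which is compatible with 5% for 200 runs (standard error 1.5 points). The moderator-only scenario has no result in this model, so that part rests on the two-arm simulation.

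**The case against.** The strongest reply is that this is loose wording in a condensed article. The section describes its models by naming variables, not terms: it does not write out the treatment by assessment point interaction for the main analysis either. The intended target is plainly moderation, the word covariates may be shorthand for entering the variables with their interactions, and the full analysis plan is not shown. That stands to this extent: it cannot be said that predictors will be reported as moderators, only that this follows if the sentence is carried out literally. It does not remove the point, because the article is not silent on method. It states one, and that one does not estimate the target.

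A second reply concerns size. The correlations are assumed, Fisher's z treats one cross-sectional correlation and not the mixed model, and the 75 to 78% is power for a genuine association that becomes an error only when it is labelled moderation. This is fair. The simulations give the same direction, but the percentages are illustrations over an assumed range. A moderator that is also prognostic could produce a significant covariate term, though that term still would not measure the change in treatment effect.

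A reader might also infer from Table 1 that post-baseline depression, alcohol or drug scores will enter the model and bias the treatment effect. The article does not say so. Table 1 is a measurement schedule, two of the five variables exist only at baseline, and the treatment-effect model has its own sentence without these variables. Which value is used is a matter for clarification.

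Finally, a reader might add that five tests at 0.05 give a 1 − 0.95⁵ = 23% chance of at least one false claim, if independent. That applies equally to five interaction tests, so it does not argue for one method over the other; it supports only an exploratory label.

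**Conclusion.** The point holds, conditional on the method being applied as written. A covariate main effect answers whether a variable is associated with SIAS across arms. Under the assumed correlation of 0.3 it would flag a non-moderating predictor in about 75 to 78% of trials (41 to 43% at 0.2), against 5% for a valid interaction test. It would detect a moderator with no average prognostic effect in about 5 to 7% of trials, close to the nominal error rate. These figures rest on assumed covariate strengths and on the article's own SD and group sizes.

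It should be fixed but is not critical. A reader might take it as a threat to the trial's main result; the documents do not support that. Moderation is not among the stated hypotheses, the sample size was not set for it, and the comparison of VR with in vivo exposure does not depend on it.

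**What to change.** Replace the covariate sentence with an interaction specification:
- For each candidate, fit a separate model containing its baseline value × treatment × assessment point and all lower-order terms, and take the contrast at post-treatment.
- Report the interaction estimate with its confidence interval.
- Label the five analyses exploratory, and describe main effects as predictors, not moderators.
- State that the baseline value is used. This is a clarification only.

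The cost is about two sentences. No new data are needed, since Table 1 already has all five variables at baseline. The price is imprecision: with 38 per arm, a moderator that changes the effect by 5 points per SD would be detected in only about 28% of trials. That is why intervals should be reported and a non-significant interaction should not be read as absence of moderation.
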